**Randomization Method:**
Block randomization with block sizes of 4, 8, and 12 will be used to ensure equal allocation. A random list is generated via Sealed Envelope. Only an external observer responsible for allocation has access to the list. Researchers are blinded and do not participate in allocation. Randomization protocol adherence will be closely monitored.

**Blinding:**
Dressings will appear identical across all groups. Since the membrane is under the dressing, participants remain blinded. Surgical teams cannot be blinded. The physician assessing wound outcomes will be blinded; another clinician will remove the dressing before assessment. Data analysts and follow-up interviewers are also blinded. Only the surgical team and allocation observer are unblinded.

**Unblinding Protocol:**
Unblinding occurs only when medically necessary, such as in the event of a serious adverse event, and only by decision of the PI or co-PI. Group codes are sealed at the study site and opened only in emergencies.

**Study Termination Policy:**
The trial will end if:

- The ethics committee requests termination due to ethical concerns
- The principal investigator decides to terminate the study

**Statistical Analysis:**
Analysis will be performed using Stata 17.0. Normality will be assessed via statistical tests, graphical evaluation, and skewness/kurtosis. One-way ANOVA and Kruskal-Wallis tests will be used for parametric and non-parametric continuous variables, respectively. Chi-square or Fisher’s Exact tests will be used for proportions. A p-value <0.05 is considered statistically significant. For participants who discontinue or are lost to follow-up, available data will be included. Interim analysis will be performed at 50% enrollment, with p < 0.001 considered significant.

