**General, Specific, and Practical Objectives**

**Main Objectives of the Study:**

1. To investigate the effect of autologous amniotic membrane on cesarean wound healing and complications
2. To investigate the effect of sprayed autologous amniotic fluid on cesarean wound healing and complications
3. To assess the effect of simultaneous use of autologous amniotic membrane and sprayed fluid on cesarean wound healing and complications
4. To compare the effects of amniotic membrane, sprayed amniotic fluid, and their combined use on cesarean wound healing and complications

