**Study Execution Method**

**Design:**
This is a prospective, interventional, randomized, controlled, factorial, and double-blind clinical trial.

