**Interventions:**

- **Group A:** Dressing with autologous amniotic membrane
- **Group B:** Dressing with sprayed autologous amniotic fluid
- **Group C:** Combination of both membrane and fluid
- **Group D (Control):** Standard dressing

In Group A, a piece of the patient's own amniotic membrane (sized to the surgical incision) is washed with sterile normal saline and placed on the wound before standard dressing. In Group B, extracted amniotic fluid is sprayed (method detailed below). Group C receives both interventions. Group D receives only standard care dressing.

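### The protocol sets up a 2x2 factorial trial but names only four-group omnibus tests, which as stated give no membrane effect, fluid effect, interaction or arm contrast

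*Protocol*

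**What the plan says.** The Design section states: "This is a prospective, interventional, randomized, controlled, factorial, and double-blind clinical trial". The project title and the methods summary also use the word factorial. Under Interventions, Group A is "Dressing with autologous amniotic membrane", Group B is "Dressing with sprayed autologous amniotic fluid", and then "Group C receives both interventions. Group D receives only standard care dressing". The protocol does not write 2x2, but those four cells are one. The Randomization Method section plans equal allocation.

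Main objective 1 is "To investigate the effect of autologous amniotic membrane on cesarean wound healing and complications", objective 2 is "To investigate the effect of sprayed autologous amniotic fluid on cesarean wound healing and complications", and objective 3 is "To assess the effect of simultaneous use of autologous amniotic membrane and sprayed fluid on cesarean wound healing and complications". Objective 4 compares the three active options. The 36 specific objectives repeat this pattern outcome by outcome.

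The Statistical Analysis section gives, for continuous outcomes, "One-way ANOVA and Kruskal-Wallis tests will be used for parametric and non-parametric continuous variables, respectively", with a normality assessment to choose between them, and chi-square or Fisher's exact tests for proportions. It names no factor term, contrast, interaction, pairwise comparison, effect estimate or confidence interval.

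**The concern.** A four-group omnibus test has three degrees of freedom and one null hypothesis: that all four groups are alike. Rejecting it does not say whether the membrane works, whether the fluid works, or whether one alters the effect of the other. Objective 4 is not answered either, because ranking membrane, fluid and combination needs contrasts between arms.

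This is more than detail a protocol may leave open, because the section does fix a method and that method does not fit the design and objectives. If the contrasts are left unstated, they may be chosen after the data are seen, across 36 specific objectives. A second, conditional cost is precision: without interaction, each product can be assessed on about 102 versus 102 women instead of 51 versus 51.

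**Working it through.** **Inputs** (Sample Size Calculation section): POSAS patient score mean 19.3, SD 7.5; POSAS observer score 20.6, SD 7.6; VAS 8, SD 1.7; alpha 5%, power 90%, 25% reduction; 51 per group before attrition. Two-sided testing is assumed because the protocol does not state sidedness.

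**1. The plan's own figure.** The two-group formula is n = 2(1.960 + 1.282)² SD² / d² per group.
- POSAS patient: d = 0.25 × 19.3 = 4.825, n = 50.8, rounded up to 51.
- POSAS observer: d = 5.15, n = 45.8, rounded up to 46.
- VAS: d = 2.0, n = 15.2, rounded up to 16.

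The largest is 51, as stated. The sample size is therefore an unadjusted comparison of two arms and does not use the factorial margins.

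**2. Standard errors** at SD 7.5 and n = 51 per cell.
- One arm versus another: 7.5 × √(2/51) = 1.49.
- Main effect (A+C versus B+D, or B+C versus A+D): 7.5 × √(1/51) = 1.05.
- Interaction (C − A − B + D): 7.5 × √(4/51) = 2.10.

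The differences detectable with 90% power are 3.242 times these: 4.81 points (24.9% of 19.3), 3.40 points (17.6%) and 6.81 points (35%).

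**3. Power**, two-sided 5%, from the noncentral t and F distributions. *Membrane only* means the fluid has no effect and there is no interaction. *Redundant* means either product gives the full benefit and the second adds nothing, so the main effect is d/2. The 18% effect (0.18 × 19.3 = 3.47 points) is an illustration; the protocol's own planning effect is 25%.

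| Scenario | Main effect | Omnibus F | A versus D |
|---|---|---|---|
| Membrane only, 18% | 91% | 79% | 64% |
| Membrane only, 25% | 99.6% | 97.9% | 90% |
| Redundant, 18% | 38% | 66% | 64% |
| Redundant, 25% | 63% | 93% | 90% |

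The main-effect analysis gains when the products do not interact and loses when they are redundant.

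**4. Power for the interaction.** For an interaction of 4.825 points, the ratio to its standard error is 4.825 / 2.10 = 2.30, giving power of about 63%. For 3.47 points it is 38%.

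**5. Event counts.** The Introduction gives 3–15% for wound complications. With 51 per arm that is 51 × 0.03 = 1.5 to 51 × 0.15 = 7.7 expected events per arm. If the risk is the same in all four arms, the chance that at least one arm has no event is 1 − (1 − (1 − p)^51)^4. This is 61% at p = 3% and 26% at p = 5%. A logistic model with an interaction term would then often have no finite estimate.

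**The case against.** One-way ANOVA on four cells is the saturated 2x2 model. Both main effects, the interaction and every arm difference are linear contrasts of it, and a statistical analysis plan not shown here could specify them. That stands. A reader might infer that the trial can never estimate the factor effects, but the documents do not support this. What they show is that the tests as named do not deliver those effects and that no contrast is stated. The rescue covers only the ANOVA. Kruskal-Wallis and the four-group chi-square or Fisher tests do not give these quantities directly, and the infection, dehiscence, hematoma and seroma outcomes are proportions.

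Much of the protocol also reads as a four-arm trial. Objective 3 is naturally C versus D, objective 4 compares arms, the sample size is per arm, and even objectives 1 and 2 could be read as A versus D and B versus D. This also stands. It means arm comparisons must not be displaced by main effects. It does not rescue the omnibus tests, which supply neither.

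A reader might further infer that the planned tests are underpowered or that factorial precision is simply wasted. Neither follows. At the planned 25% effect every approach in the membrane-only scenario has about 90% power or more, and under redundancy the ranking reverses. Additivity cannot be presumed for two products from the same amnion applied to the same wound.

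**Conclusion.** The point holds as a mismatch between the analysis section and the protocol's own design and objectives. The omnibus tests, as the only stated methods, answer none of main objectives 1 to 4.

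The precision argument is secondary and conditional: a standard error of 1.05 against 1.49 points, assuming SD 7.5, 51 evaluable women per arm and no material interaction. The trial could not rule such an interaction in or out reliably, with about 63% power for one as large as the planning difference of 4.825 points.

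The sample size is not called into question. Fifty-one per group gives about 90% power for one pairwise comparison at the planned effect, before any multiplicity adjustment.

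**What to change.** Amend the Statistical Analysis section as follows.

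- **Continuous outcomes:** fit a linear model with membrane (yes/no), fluid (yes/no) and their product. Report both main effects and the interaction with 95% CIs. From the same model always report A−D, B−D, C−D, A−B, A−C and B−C. Do not make these conditional on the interaction result, because objectives 3 and 4 ask for arm comparisons and the interaction test has limited power.
- **Infection, dehiscence, hematoma, seroma:** report risk differences with 95% CIs by factor margin and by arm, with Fisher's exact test. Fit a binomial or logistic model with an interaction term only where event counts allow, and state that condition in advance.
- **Interpretation:** state that the gain in precision depends on there being no material interaction, that power is about 63% for an interaction of 4.825 points, and that 51 per group still gives about 90% power for an unadjusted pairwise comparison at the 25% effect.

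The cost is analysis wording and programming in the Stata version already named, with no new patients, visits or data. The downside is that main effects average over the other factor and can mislead if the products interact, which is why the arm comparisons are always shown.

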**Specific Objectives of the Study:**

1. To assess the effect of amniotic membrane on wound healing using the POSAS scale on days 10 and 28 post-surgery
2. To evaluate the effect of amniotic membrane on surgical site infection
3. To assess the effect of amniotic membrane on wound dehiscence
4. To assess the effect of amniotic membrane on hematoma formation
5. To assess the effect of amniotic membrane on seroma formation
6. To assess the effect of amniotic membrane on pain at 4, 12, 24, and 36 hours after surgery
7. To assess the effect of amniotic membrane on the frequency of injected analgesic use in the first 36 hours
8. To evaluate the effect of amniotic membrane on the incidence of any adverse events
9. To assess the effect of amniotic membrane on the duration of hospitalization
10. To assess the effect of sprayed amniotic fluid on wound healing using the POSAS scale on days 7 and 28 post-surgery
11. To evaluate the effect of sprayed amniotic fluid on surgical site infection
12. To assess the effect of sprayed amniotic fluid on wound dehiscence
13. To assess the effect of sprayed amniotic fluid on hematoma formation
14. To assess the effect of sprayed amniotic fluid on seroma formation
15. To assess the effect of sprayed amniotic fluid on pain at 4, 12, 24, and 36 hours after surgery
16. To assess the effect of sprayed amniotic fluid on the frequency of injected analgesic use in the first 36 hours
17. To evaluate the effect of sprayed amniotic fluid on the incidence of any adverse events
18. To assess the effect of sprayed amniotic fluid on the duration of hospitalization
19. To assess the combined effect of membrane and fluid on wound healing using the POSAS scale on days 10 and 28
20. To evaluate the combined effect on surgical site infection
21. To assess the combined effect on wound dehiscence
22. To assess the combined effect on hematoma formation
23. To assess the combined effect on seroma formation
24. To assess the combined effect on pain at 4, 12, 24, and 36 hours post-surgery
25. To assess the combined effect on the frequency of injected analgesic use in the first 36 hours
26. To evaluate the combined effect on the incidence of adverse events
27. To assess the combined effect on hospital stay duration
28. To compare the effects of membrane vs. fluid on wound healing (POSAS) on days 10 and 28
29. To compare membrane, fluid, and combination regarding surgical site infection
30. To compare the groups regarding wound dehiscence

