31. To compare the groups regarding hematoma formation
32. To compare the groups regarding seroma formation
33. To compare the groups regarding pain at 4, 12, 24, and 36 hours post-surgery
34. To compare the groups regarding injected analgesic use in the first 36 hours
35. To compare the groups regarding adverse events
36. To compare the groups regarding length of hospital stay

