**Sample Size Calculation:**
Based on the study by Cromi et al. (16), which compared cesarean wound healing and pain across four suturing techniques, the following assumptions were made:

- POSAS patient score mean = 19.3 (SD = 7.5)
- POSAS observer score mean = 20.6 (SD = 7.6)
- VAS mean pain score = 8 (SD = 1.7)
  With a significance level (alpha) of 5% and power of 90% to detect a 25% reduction in wound healing and pain scores, the highest calculated required sample size was 51 per group. Allowing for a 10% attrition rate, the final sample size is set at 56 participants per group, totaling 224 participants across four groups.

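### No primary outcome, time point or comparison is named, and one p<0.05 rule covers 36 unranked objectives, so the trial's false-positive rate is well above 5%

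*Protocol*

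**What the plan says.** Main Objectives of the Study gives four aims, each on the broad pair of wound healing and complications. The first is "To investigate the effect of autologous amniotic membrane on cesarean wound healing and complications" and the last is "To compare the effects of amniotic membrane, sprayed amniotic fluid, and their combined use on cesarean wound healing and complications". No scale or visit is attached to any of them.

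Specific Objectives of the Study expands these into 36 items of equal rank. Nine outcomes (POSAS, surgical site infection, dehiscence, hematoma, seroma, pain, injected analgesic use, adverse events, hospital stay) are each taken up four times: for membrane, for fluid, for the combination, and as a comparison between groups. The list ends with "To compare the groups regarding length of hospital stay". POSAS is assessed twice, as in "To assess the effect of amniotic membrane on wound healing using the POSAS scale on days 10 and 28 post-surgery", and pain four times, at 4, 12, 24 and 36 hours.

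Sample Size Calculation uses patient POSAS, observer POSAS and VAS pain, takes the largest resulting n, and gives no visit for any of the three.

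Statistical Analysis names the tests, "One-way ANOVA and Kruskal-Wallis tests will be used for parametric and non-parametric continuous variables, respectively", with chi-square or Fisher's exact tests for proportions, and sets the threshold: "A p-value <0.05 is considered statistically significant". The interim rule, "Interim analysis will be performed at 50% enrollment, with p < 0.001 considered significant", names no outcome either.

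**The concern.** A 5% significance level controls a trial's false-positive rate only when it attaches to a known decision. Here any of several scales, visits or arms could become the headline result after the data are seen, and nothing in the protocol would contradict that choice. A reader of the final report could not tell a planned finding from a selected one.

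The sample size does not resolve this. It gives each of three scores at least the stated power, but it does not say which of them, or which visit, decides the trial.

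**Working it through.** **Step 1: the plan's own figure.** Inputs from Sample Size Calculation: alpha 5% (two-sided assumed), power 90%, a 25% reduction, and the three means and SDs. For two groups, n per group = 2 × [SD × (1.960 + 1.282) / difference]².

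- Patient POSAS: difference 0.25 × 19.3 = 4.825, SD 7.5, n = 50.8, so 51.
- Observer POSAS: difference 0.25 × 20.6 = 5.15, SD 7.6, n = 45.8, so 46.
- VAS: difference 0.25 × 8 = 2.0, SD 1.7, n = 15.2, so 16.

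The largest is 51, as stated, and patient POSAS alone sets it. The calculation is for one two-group comparison of one score at 5%. (The attrition step, 51/0.9 = 56.7, rounds up to 57 rather than 56; this is immaterial here.)

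**Step 2: counting the tests.**

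- Four-group tests only, one per outcome: 9.
- The same, with both POSAS scores at two visits (4), pain at four times (4) and the other seven outcomes once each (7): 15.
- Adding each of the three active arms against control: 9 × 4 = 36, or 15 × 4 = 60.

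**Step 3: independent tests as a ceiling.** Chance of at least one p<0.05 = 1 − 0.95^k: 37% for k = 9, 54% for 15, 84% for 36, 95% for 60. The real tests share patients, a control arm and related outcomes, so these figures are upper guides only.

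**Step 4: simulation under no effect.** Four arms of 51; 15 endpoints, of which 10 are continuous and 5 binary with event rates of 3-15%; analysis of variance and chi-square across four groups; t tests and Fisher's exact test for each arm against control; 3,000 replicates (standard error about 0.9 percentage points near 50%). Where one time point per outcome was used, patient POSAS at the later visit and pain at 24 hours were taken.

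| Correlation within / between outcome domains | 9 four-group tests | 15 four-group tests | 36 tests | 60 tests |
|---|---|---|---|---|
| 0 / 0 | 33% | 52% | 57% | 82% |
| 0.3 / 0.1 | 33% | 49% | 56% | 80% |
| 0.5 / 0.2 | 34% | 48% | 57% | 78% |
| 0.7 / 0.3 | 31% | 41% | 52% | 68% |
| 0.8 / 0.5 | 30% | 37% | 49% | 62% |

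**Step 5: power under two possible remedies, for patient POSAS.** The standardized difference is 4.825/7.5 = 0.643.

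- Two main effects at 0.025 each. With 10% attrition, 224 × 0.9 is about 200 analyzed, so about 100 v 100 for each factor. Power = Φ(0.643 × √50 − 2.241), about 0.99, if each main effect is the full 25% reduction and there is no interaction.
- Three arms against control at 0.05/3 = 0.0167. With 51 per group, power = Φ(0.643 × √25.5 − 2.394), about 0.80. Restoring 90% needs 66 per group, or 66/0.9 = 73.3, so 74 with attrition: 296 in total.

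**The case against.** Three arguments carry weight.

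First, Statistical Analysis names only four-group tests and no pairwise ones. Read literally, that is 9 to 15 tests, not 36 to 60. This stands as a reading, and it is why the lower range is reported. It does not remove the problem: 30-52% is still six to ten times the nominal rate, and a four-group test cannot answer objectives 1-27, which ask what membrane, fluid and their combination each do.

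Second, a multiplicity method and a testing hierarchy commonly sit in a statistical analysis plan, which is not at hand, and the p<0.05 sentence is conventional. Both are true, so the absence of an adjustment method is not the point. The choice of primary outcome and visit belongs in the protocol because the sample size depends on it, and this protocol fixed its objectives, sample size and threshold without making that choice.

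Third, sizing on the largest of three requirements is not an error. That is correct: it protects power for each score. It simply does not identify a primary outcome.

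**Conclusion.** The point holds. The protocol defines no primary outcome, time point or comparison, and its single threshold does not hold the trial's false-positive rate at 5%. Under no effect, the chance of at least one p<0.05 in either direction is about 30-52% with the named four-group tests alone and about 49-82% with the contrasts that the objectives need. The assumptions not taken from the document are two-sided testing, the correlations, and the event rates of the individual binary outcomes.

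A reader might infer that all 36 objectives are certain to be tested separately, and that a false claim of benefit is therefore likely, with 84% as its size. The documents do not support that. No pairwise tests are specified. The 84% treats the tests as independent and each as having an exact 5% error rate, although five of the nine outcomes are binary; with event rates of 3-15%, Fisher's exact test at this sample size rejects well below 5% of the time. It also counts results that show harm. Counting only results that favor the intervention, 36 tests at 0.025 give 1 − 0.975^36 = 60% if independent and about 38% and 28% at common correlations of 0.3 and 0.5. These are rough figures, since nine of the objectives have no simple direction. An inflated error rate is established; a probable false claim of benefit is not.

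**What to change.** Before any data are seen, amend the protocol as follows.

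- **Name one primary outcome at one visit.** Patient POSAS fits the existing sample size. The visit, for example day 28, is the sponsor's choice, because the sample-size section gives none. The early visit would first need one label, since it appears as day 7, day 10 and week 1 in different sections.
- **State the primary comparison or comparisons and share the 5% among them.** One option is the membrane and fluid main effects in a two-factor model, at 0.025 each or by Holm's method, with about 99% power under the conditions in the working. The other is three arms against control at 0.0167 each; the stated power should then be changed to about 80% at 51 per group, or the trial enlarged.
- **Report all other outcomes as secondary**, with estimates and 95% confidence intervals and no confirmatory claims.
- **Tie the interim rule to the same primary outcome.**

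Costs: the primary analysis replaces the one-way test now planned, so this is more than a change of wording. Secondary findings become supportive. Under the main-effects option, the objectives on the combination and on comparisons between interventions have no confirmatory test. That option needs no additional patients; the three-comparison option does, if 90% power is to be kept.

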**Summary of Method and Analysis Techniques:**
This study is a prospective, interventional, randomized, controlled, factorial, double-blind clinical trial conducted at Arash Women's Hospital among pregnant women scheduled for cesarean section. The intervention groups are:

- Group A: Dressing with autologous amniotic membrane
- Group B: Dressing with autologous amniotic fluid spray
- Group C: Combination of autologous membrane and fluid spray
- Group D: Standard cesarean wound dressing (control)

Amniotic fluid and membrane are obtained from the patient herself and applied at each wound closure stage. Outcomes will be assessed on postoperative days 2, 10, and 28.

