**Timeline Table**

| **Row** | **Implementation Stage** | **Total Duration** |
| --- | --- | --- |
| 1 | Proposal approval | 1 month |
| 2 | Registration in IRCT | 2 months |
| 3 | Patient recruitment and study execution | 8 months |
| 4 | Analysis and final report presentation | 1 month |

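### The single interim threshold of p < 0.001 carries no direction and no outcome, so it also governs complications, where 112 women give it almost no ability to flag harm

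*Protocol*

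**What the plan says.** The protocol, under Statistical Analysis, plans one interim look: "Interim analysis will be performed at 50% enrollment, with p < 0.001 considered significant". The sentence does not say which outcomes are examined, in which direction, at what data cut-off, or who receives the result. The same section assigns ANOVA or Kruskal-Wallis to continuous outcomes and chi-square or Fisher tests to proportions, with 0.05 as the general significance level.

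The sample size section gives a trial "totaling 224 participants across four groups", sized on scar and pain scores: "With a significance level (alpha) of 5% and power of 90% to detect a 25% reduction in wound healing and pain scores". The Timeline Table allots 8 months to "Patient recruitment and study execution". The method summary states "Outcomes will be assessed on postoperative days 2, 10, and 28", and the Follow-Up Schedule records infection signs and adverse events at discharge, at days 8–12 and at week 4.

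The Study Termination Policy lists two routes to ending the trial: "The ethics committee requests termination due to ethical concerns", or a decision of the principal investigator. Neither route is tied to a scheduled review of data by group.

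**The concern.** A threshold of 0.001 at half enrolment is a sensible guard against stopping early for apparent benefit. It is a poor rule for harm, because it asks for the same extreme evidence before an excess of complications counts. The protocol states one number without limiting it to benefit, and it names tests that would carry that number over to infection, dehiscence, hematoma and seroma. The trial was sized on POSAS and VAS, not on complications.

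This is the only planned comparison by group before the end of the trial. Adverse events are recorded at each visit, but the outcome assessor, interviewers and analysts are blinded, so a modest imbalance between groups would not show in case-by-case recording. A result labelled not significant could then be taken as reassurance while the remaining 112 women are enrolled.

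A lesser matter is that the trigger is enrolment, while outcomes run to day 28. Some of the 112 women will not have had their last visit.

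**Working it through.** **Inputs.** From the protocol: 224 women, 56 per group, equal allocation; interim at 50%, so 112 women, 28 per group, or 56 v 56 for each factor (membrane or not, fluid or not); threshold 0.001; 8 months; last assessment at day 28. Assumed: two-sided tests (sidedness is not stated), even recruitment, and infection rates of 5% v 15%. The Introduction puts wound complications, including infection, at 3–15%.

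**1. The plan's own sample size.** "POSAS patient score mean = 19.3 (SD = 7.5") gives a 25% reduction of 0.25 × 19.3 = 4.825. Then n = 2 × [(1.960 + 1.282) × 7.5 / 4.825]² = 50.8, so 51 per group. "POSAS observer score mean = 20.6 (SD = 7.6") gives 45.8, so 46; VAS (8, SD 1.7) gives 15.2, so 16. The stated maximum of 51 is reproduced. For attrition, 51 × 1.1 = 56.1 and 51/0.9 = 56.7; the stated 56 is close enough for this purpose.

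**2. What the threshold demands for a complication.** Take 2 events in the comparison group and find the smallest treated count with two-sided Fisher p < 0.001.
- Factor, 56 v 56: 15/56 gives p = 0.00102, which fails; 16/56 (29%) gives p = 0.0005, which passes.
- One group v control, 28 v 28: 13/28 gives p = 0.0019, which fails; 14/28 (50%) gives p = 0.0008, which passes.

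**3. Chance of flagging a real excess.** Exact power is the sum of the two binomial probabilities over all tables with Fisher p < 0.001. For 5% v 15%:

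| Comparison | Complete follow-up | Only women past week 4 (about three quarters) |
|---|---|---|
| Factor | 2.6% (56 v 56) | 0.8% (43 v 43) |
| Group v control | 0.15% (28 v 28) | 0.01% (21 v 21) |

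A four-group chi-square with 28 per group, two groups at 5% and two at 15%, crosses 0.001 about 1.5% of the time (simulation). The choice among the named tests does not change the picture.

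**4. Women short of week 4 at the trigger.**
- Recruitment over the full 8 months: 224 / 243.5 days = 0.92 per day; × 28 = 25.8 women; 25.8/112 = 23%.
- If the 8 months include the last 28 days of follow-up: 224 / 215.5 = 1.04 per day; × 28 = 29.1 women; 29.1/112 = 26%.
- Women with week-4 data: 112 − 29 to 112 − 26 = 83 to 86, which is 37–38% of 224.

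The share is 18% if recruitment takes 10 months, 31% if 6 months, and 30–40% if accrual ramps up or is front-loaded. Only about 8–11% would also lack the day 8–12 visit.

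**5. Type I error.** With a look at 0.001 at half information and a final test at 0.05, the overall two-sided error for one comparison is 0.0502. The look costs practically nothing there.

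**The case against.** The strongest reply is that the sentence is silent rather than wrong. It fixes a milestone and a threshold, and the outcomes, cut-off and recipients may sit in a SAP that is not shown. That stands for the cut-off and the recipients. It does not fully answer the threshold, which the protocol states without restriction in the section that names the tests for proportions.

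The reply also notes that this is not the trial's only test of complications (the final analysis uses 0.05), and that the ethics committee or principal investigator can stop the trial at any time. Both are correct. The point concerns the only planned between-group look during recruitment.

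Three stronger readings are tempting, and the documents do not support them.
- A reader might infer that women awaiting their week-4 visit are counted as event-free, because the section says available data will be included. That sentence concerns women who discontinue or are lost to follow-up, not women whose visit is still due.
- A reader might blame the enrolment trigger for missed harm. The power is 2.6% or 0.15% with complete follow-up, so the threshold is the cause. Blocked equal allocation makes the missing follow-up similar across groups, and only events first seen after the day 8–12 visit are affected.
- A reader might infer that the ethics committee is denied the look. The protocol does not say who receives it.

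Finally, if safety is the worry, delaying the look to complete follow-up works against it. That is fair, and the fix respects it.

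**Conclusion.** The point holds as a cheap improvement to a rule that is stated too broadly. Followed as written, the interim rule would call even a threefold excess of infection not significant almost every time: about 97% of the time for a factor (100 − 2.6) and more than 99% for one group against control (100 − 0.15). This rests on the assumed 5% and 15% rates and on two-sided tests. The required counts of 16/56 and 14/28 depend only on the threshold, the two-sided Fisher test and 2 events in the comparison group.

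The incomplete follow-up is secondary. About a quarter of week-4 data would be outstanding under even recruitment, which reduces information without biasing the comparison. The protocol promises 50% enrolment, not 50% information, so the 37–38% contradicts nothing in it.

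**What to change.** In the Statistical Analysis section:
1. Limit p < 0.001 to benefit on the healing and pain outcomes.
2. At the same look, give the ethics committee counts and percentages with 95% intervals for infection, dehiscence, hematoma, seroma and serious adverse events, by group and for each factor, with no significance threshold for harm.
3. State the data cut-off, and use as denominator for week-4 outcomes only women who have completed or passed that visit.

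A matching line in the Study Termination Policy should say that the committee receives this table. The efficacy test may wait until the first 112 women have passed week 4, but the safety table should go out at the 50% enrolment point.

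The cost is a few sentences and one table from data already collected. If the efficacy test waits, it comes about four weeks later, with some 26 to 29 more women enrolled by then (about 138 to 141 in all).
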